## Stopping rules

The trial will be stopped if the Data Safety Monitoring Board (DSMB) believes there is an unacceptable risk of serious adverse events in one or more of the treatment arms. No interim analyses of efficacy are planned to there are no formal stopping rules for efficacy or futility.

## Statistical issues

### Sample size and the detectable difference

The sample size was selected to have adequate power to detect a clinically significant difference of 2.0 points between groups on the Roland Disability scale. Our target sample size of 640 randomized individuals (160 per group) was computed using assumptions described below. Assuming 10% loss to follow-up for each group, there will be outcome data for 144 participants per group. The power of the overall analysis depends on how the four means are distributed. We used the pilot data to estimate the distribution of the means for the four groups and then computed an effect size that was used in the omnibus power calculation.

In the proposed analysis we will first determine if there is an overall difference among the four treatment groups using a two-sided significance level of 0.05. With 144 per group, this omnibus F-test will have 99% power for detecting a statistically significant difference among the four treatment means given the effect size obtained in the pilot study. If this omnibus test is statistically significant, we will compare specified pairs of means as indicated in the proposal. Because this will involve multiple post-hoc comparisons, we will use the Tukey-Kramer multiple comparisons procedure [36] to allow for all possible pairwise comparisons holding the overall α = 0.05. We will not consider a pairwise difference between the means to be statistically significant unless the t-value exceeds 2.61, instead of the usual 1.96.

Both primary outcomes (Roland Disability Questionnaire and bothersomeness of low back pain) are tested at the 0.05 level because they address separate scientific questions. The analyses of covariance of the 8-week pilot data provided estimates of the standard deviations of the primary outcome measures adjusted for pre-randomization baseline values: Roland SD = 4.71 and Bothersomeness SD = 2.73. Using these assumptions, the power to detect a pairwise difference of 2.0 Roland units is 84%, adjusted for multiple comparisons. For the bothersomeness outcome, for which a difference of 1.5 points is considered minimally clinically significant, we will have 98% power to detect a difference of this magnitude. Thus, if our assumptions are correct, 160 participants per group will provide adequate power to detect the smallest clinically meaningful differences on both of our primary outcome measures even after adjustment for multiple pairwise comparisons.

In our secondary analyses, we will compare the proportions of participants in each treatment group who experience clinically significant improvement on our primary outcome measures.

We plan to conduct subgroup analyses of gender, study site, and race/ethnicity that will include an overall comparison of the four groups followed by specific pairwise comparisons. Power for some of these comparisons will be limited. While we will test a site by treatment interaction to determine if the treatment effects differ across the two sites, this test will only be sensitive to very pronounced effect modification by site.

In summary, we have high power to find an overall difference among the four groups even in some of the planned subset analyses. Although powered to detect clinically significant difference on the Roland Disability scale, the resultant sample size will provide ample power for our other primary outcome, bothersomeness of back pain, even in pairwise comparisons adjusted for multiple comparisons. Because our estimates are conservative, we are very likely to have adequate power even if the assumptions on which our power estimates are based prove incorrect. In addition, the proposed sample sizes will permit us to explore whether the findings apply equally to women and men and to different racial groups.

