## Methods and design

### Overview

Eligible participants at two sites will be randomized equally to one of four treatments: individualized acupuncture point stimulation, standardized acupuncture point stimulation, non-insertive simulated acupuncture point stimulation, or usual care (Figure 1). Participants in all three "acupuncture" arms will receive 10 "treatments" involving stimulation of acupuncture points over a 7-week treatment period (two treatments per week for 3 weeks, weekly treatments for 4 weeks).

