### Statistical analysis

The power calculations are based on simple comparisons of the follow-up scores at a single point in time (eight weeks after randomization) with adjustment for baseline values using analysis of covariance. We also plan to adjust for other baseline characteristics. In a large randomized trial, baseline values and other covariates are unlikely to differ across randomized groups. However, for continuous outcome data, inclusion of baseline covariates can improve precision of the variance estimate and therefore increase power. The covariates to be used in the final model will be based on past experience and model fit as assessed prior to inclusion of treatment group in the model. We will use the Tukey-Kramer method to adjust for multiple pairwise comparisons [36] across the four groups and allow all pairwise comparisons to be conducted holding the overall α = 0.05 fixed.

We will use an intent-to-treat approach to all analyses, i.e. individuals will be analyzed by randomized group regardless of participation in any treatment sessions. This minimizes biases that often occur when participants not receiving assigned treatments are excluded from analyses. Furthermore, we will adjust for geographic site as a main effect. The standard linear regression model (ANCOVA) is of the form:

*Y*(*t*) = *β*_0 _+ *β*_1 _*Baseline *+ *α*_1 _Grp1+ + *α*_2 _Grp2 + *α*_3 _Grp3 + *θ*^*T *^*z *+ *ε*

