where response is at follow-up time t, baseline is the pre-randomization value of the outcome measure, z is a vector of covariates representing other variables being adjusted for, including geographic site and, for some models, visits to various providers for back pain as part of usual care. The referent group is Usual Care in this model. We will consider interactions of treatment and the baseline value that would indicate that the effect of treatment depends on status at baseline. We will also test for significant interactions of treatment with other variables (e.g. site, race, gender) to determine if treatment differences are modified by these variables. The statistical model assumes that the error terms are normally distributed. In previous studies we have used transformations when this assumption was not satisfied. However, given that these patients have chronic back pain it is unlikely that most will return to a level of no pain or dysfunction so floor effects are not expected to be large. We will also investigate whether there are differences among the treating acupuncturists by inclusion of acupuncturist in the model as a random effect.

If we find a significant overall difference among the four groups for a particular outcome, we will localize the difference using pairwise comparisons in accordance with our specific aims (see Section 2 Project Overview). We will use the Tukey-Kramer procedure to adjust for multiple comparisons while maintaining an overall significance level of 0.05. Each specific aim will be addressed by a specific pairwise comparison.

Although this model evaluates differences at one time-point it can be extended to include all follow-up times to assess whether treatment effects change over time. This would be indicated by significant time by treatment interactions. For longitudinal analyses, we would use a generalized estimating equation (GEE) approach to protect against misspecification of the correlation within a participant's scores over time. Such analyses can incorporate every time point completed by a participant. However, it is important to assess whether there is differential drop-out by either assigned treatment or symptom or function level. If differential drop-out occurs, we will use the method of Little to rectify possible biases that could occur [37].

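### The fixed pairwise cutoff of t > 2.61 is not the Tukey-Kramer 0.05 value for this trial, which is about 2.58; the error is small and conservative

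*Protocol article*

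**What the plan says.** The rule is set out in the protocol article under Sample size and the detectable difference, and repeated in part under Statistical analysis.

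- **First step.** An F-test looks for an "overall difference among the four treatment groups using a two-sided significance level of 0.05".
- **Precondition.** "If this omnibus test is statistically significant, we will compare specified pairs of means as indicated in the proposal".
- **Pairwise procedure.** Tukey-Kramer is chosen "to allow for all possible pairwise comparisons holding the overall α = 0.05". Statistical analysis names the same method and level, again to "allow all pairwise comparisons to be conducted holding the overall" level fixed, and gives no numeric cutoff there.
- **Numeric cutoff.** A pairwise difference will not be called significant "unless the t-value exceeds 2.61, instead of the usual 1.96". No degrees of freedom are given for this number.
- **Power.** Pairwise power is given as 84% for 2.0 Roland points and 98% for 1.5 bothersomeness points, adjusted for multiple comparisons. Power of the F-test is reported separately as 99%, using an effect size from pilot means that the article does not list.

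**The concern.** The article defines significance on the primary endpoint in two ways: by a named procedure at a named error level, and by a fixed number. The two should be the same rule. If the number does not follow from the procedure at this sample size, a contrast can pass one rule and fail the other. Choosing between them once the data are known would look data-driven, even if done in good faith.

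A second question is what the pairwise power describes. The plan permits pairwise tests only after a significant F-test, so a reader needs to know whether the 84% and 98% already include that step.

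**Working it through.** **Inputs** (protocol article, Sample size and the detectable difference, unless noted)

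- Four arms, equal allocation (Overview); 160 randomized and 144 analysed per arm after 10% loss, so 4 × 144 = 576 analysed.
- Error degrees of freedom: 576 − 4 = 572 before covariates; about 570 with the baseline value and site in the model.
- Adjusted SDs: Roland 4.71, bothersomeness 2.73. Differences of interest: 2.0 and 1.5 points.

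**1. Reproduce the stated power from 2.61**

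Standard error of a pairwise difference = SD × √(2/144). Power ≈ Φ(difference/SE − critical t).

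- Roland: SE = 4.71 × 0.11785 = 0.555; 2.0/0.555 = 3.603; Φ(3.603 − 2.61) = Φ(0.993) = 84.0% (noncentral t: 83.9%). Stated: 84%.
- Bothersomeness: SE = 2.73 × 0.11785 = 0.322; 1.5/0.322 = 4.662; Φ(4.662 − 2.61) = Φ(2.052) = 98.0% (noncentral t: 98.0%). Stated: 98%.

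Both figures reproduce from the pairwise test at 2.61 alone, with no F-test step.

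**2. The Tukey-Kramer critical t**

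With equal groups it is q(0.95; 4 groups, df)/√2, where q is the studentized range quantile.

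| Error df | Critical t |
|---|---|
| 100 | 2.613 |
| 120 | 2.605 |
| 200 | 2.591 |
| 572 (570 and 566 agree to three decimals) | 2.577 |
| 636 (all 640 analysed) | 2.576 |
| infinite | 2.569 |

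Extra covariates or complete follow-up do not bring the value near 2.61. Other standard adjustments at 572 df do not give it either: Bonferroni for six pairs 2.647, Šidák 2.640, Bonferroni for five 2.584, Scheffé 2.804.

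**3. Family-wise error actually delivered**

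The studentized range tail beyond 2.61 × √2 = 3.691 at 572 df is 0.0458. With the F-test precondition added (F > 2.620 on 3 and 572 df), simulation of 1,000,000 trials with all four means equal gives about 0.040. With 2.577 the values are 0.050 without the precondition and about 0.042 with it.

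**4. Power at the correct critical value, pairwise test alone**

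- Roland: Φ(3.603 − 2.577) = Φ(1.026) = 84.8% (noncentral t: 84.7%).
- Bothersomeness: Φ(4.662 − 2.577) = Φ(2.085) = 98.1% (noncentral t: 98.1%).

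**5. What the F-test precondition takes away**

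The pilot means are not given, so the positions of the other two means are assumptions. Roland, two arms 2.0 points apart, 1,000,000 trials per pattern:

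| Other two means | F-test power | At 2.61: without → with F-test | At 2.577: without → with F-test |
|---|---|---|---|
| Both midway | 86.8% | 84.0 → 82.9% | 84.8 → 83.3% |
| Equally spaced | 90.3% | 83.9 → 83.3% | 84.7 → 83.9% |
| One arm differs from three | 97.1% | 83.9 → 83.8% | 84.7 → 84.6% |
| Two versus two | 99.5% | 83.9 → 83.9% | 84.7 → 84.7% |

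The cost on Roland runs from nil to 1.1 points at 2.61, and from nil to about 1.5 points at 2.577. For bothersomeness it is at most 0.3 points at either cutoff.

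**The case against.** The strongest reply is that this makes almost no difference. Both departures are conservative, the stated power is reproduced, and all the six-pair variants on Roland lie between about 82.8% and 84.7%, above the 80% that the abstract promises for most pairs. The number appears once, in the sample size section. An analyst who follows Statistical analysis would run Tukey-Kramer at 0.05 and obtain the right critical value without ever using 2.61. All of that stands, and it is why the point is minor. It does not remove the point, because the sentence with 2.61 is worded as a decision rule and not as a planning approximation.

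Three stronger readings are tempting, and the documents do not support them.

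- **The power or sample size is wrong.** It is not: 84% and 98% follow from the stated inputs, and the correct cutoff moves them up by 0.8 and about 0.1 points.
- **The F-test precondition is an error that the 84% conceals.** Tukey-Kramer does hold the family-wise level without a preceding F-test, so the step is not needed for that purpose. But it is a prespecified, conservative convention, and it blocks false positives as well as true ones (4.6% to 4.0% under the global null). The article reports F-test power and pairwise power separately and does not call the 84% a joint figure. The largest loss also needs a pattern with F-test power of 87%; in the two-versus-two pattern, where it is close to the stated 99%, the loss is essentially nil.
- **The adjustment should cover only the four contrasts in the hypotheses.** The article does say "Each specific aim will be addressed by a specific pairwise comparison", and a four-contrast family would have a critical t of about 2.45 and Roland power of about 87.5%. But both statistical sections deliberately cover all pairs, and the question in Aim 2 concerns needling in general against simulated treatment, which brings in a fifth contrast. Narrowing the family would be a different design.

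**Conclusion.** The cutoff of 2.61 is inconsistent with the procedure and level that the article names. At about 570 error degrees of freedom the Tukey-Kramer value is 2.577, and a fixed 2.61 delivers a family-wise error of 4.6% (about 4.0% with the F-test precondition) in place of 5%. The two rules give different answers only for t between 2.58 and 2.61, which is worth about 0.8 points of power on Roland and about 0.1 on bothersomeness. Type I error is not inflated, and neither the sample size nor the conclusion that power is adequate is affected.

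This rests on the article's own 144 per arm, equal allocation and adjusted SDs. The critical value barely depends on the covariates chosen or on the exact follow-up rate. The cost of the F-test precondition does depend on assumed means and can only be given as a range.

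**What to change.** 1. In Sample size and the detectable difference, replace the 2.61 criterion with: Tukey-Kramer adjusted p < 0.05 at the model's error degrees of freedom (critical t about 2.58). This makes it one rule with Statistical analysis.
2. Restate pairwise power as about 85% for Roland and 98% for bothersomeness.
3. Add that these figures are for the pairwise test alone and exclude the F-test precondition, which lowers Roland power by between nil and about 1 point (up to about 1.5 at the corrected cutoff in the least favourable pattern tried), depending on the other means.

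The cost is wording only: no participants, no new data and no change to the analysis model. It should be settled before outcomes are compared by arm. Dropping the F-test precondition or restricting the family to named contrasts may be considered as design options, but neither is needed to correct this point.

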### Statistical analysis

The power calculations are based on simple comparisons of the follow-up scores at a single point in time (eight weeks after randomization) with adjustment for baseline values using analysis of covariance. We also plan to adjust for other baseline characteristics. In a large randomized trial, baseline values and other covariates are unlikely to differ across randomized groups. However, for continuous outcome data, inclusion of baseline covariates can improve precision of the variance estimate and therefore increase power. The covariates to be used in the final model will be based on past experience and model fit as assessed prior to inclusion of treatment group in the model. We will use the Tukey-Kramer method to adjust for multiple pairwise comparisons [36] across the four groups and allow all pairwise comparisons to be conducted holding the overall α = 0.05 fixed.

We will use an intent-to-treat approach to all analyses, i.e. individuals will be analyzed by randomized group regardless of participation in any treatment sessions. This minimizes biases that often occur when participants not receiving assigned treatments are excluded from analyses. Furthermore, we will adjust for geographic site as a main effect. The standard linear regression model (ANCOVA) is of the form:

*Y*(*t*) = *β*_0 _+ *β*_1 _*Baseline *+ *α*_1 _Grp1+ + *α*_2 _Grp2 + *α*_3 _Grp3 + *θ*^*T *^*z *+ *ε*

where response is at follow-up time t, baseline is the pre-randomization value of the outcome measure, z is a vector of covariates representing other variables being adjusted for, including geographic site and, for some models, visits to various providers for back pain as part of usual care. The referent group is Usual Care in this model. We will consider interactions of treatment and the baseline value that would indicate that the effect of treatment depends on status at baseline. We will also test for significant interactions of treatment with other variables (e.g. site, race, gender) to determine if treatment differences are modified by these variables. The statistical model assumes that the error terms are normally distributed. In previous studies we have used transformations when this assumption was not satisfied. However, given that these patients have chronic back pain it is unlikely that most will return to a level of no pain or dysfunction so floor effects are not expected to be large. We will also investigate whether there are differences among the treating acupuncturists by inclusion of acupuncturist in the model as a random effect.

If we find a significant overall difference among the four groups for a particular outcome, we will localize the difference using pairwise comparisons in accordance with our specific aims (see Section 2 Project Overview). We will use the Tukey-Kramer procedure to adjust for multiple comparisons while maintaining an overall significance level of 0.05. Each specific aim will be addressed by a specific pairwise comparison.

Although this model evaluates differences at one time-point it can be extended to include all follow-up times to assess whether treatment effects change over time. This would be indicated by significant time by treatment interactions. For longitudinal analyses, we would use a generalized estimating equation (GEE) approach to protect against misspecification of the correlation within a participant's scores over time. Such analyses can incorporate every time point completed by a participant. However, it is important to assess whether there is differential drop-out by either assigned treatment or symptom or function level. If differential drop-out occurs, we will use the method of Little to rectify possible biases that could occur [37].

We will also analyze secondary outcomes: costs of back care, general health status (SF-36), pain intensity, disability days, and satisfaction with care. An analysis of costs may entail a transformation (e.g., log cost) but can be modeled using linear regression. The model is similar to the one described above except that we will not enter a baseline value for costs in the model since this is unknown. We will adjust for age and other factors that may affect costs. For binary outcomes (e.g., participants spending any days in bed due to their back pain during the past week) we will use logistic regression. Despite the multiplicity of analyses, we will focus our analyses on the effects of the treatments on each of the five outcome domains recommended for studies of low back pain [26].

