We hypothesize that standardized acupuncture needling will be more effective than non-insertive simulated needling.

3) Is individualized acupuncture needling more effective than standardized acupuncture needling for reducing dysfunction or symptom bothersomeness due to chronic low back pain?

We hypothesize that individualized acupuncture needling will be more effective than standardized acupuncture needling.

Our secondary aims are to compare the effects of these four treatments on general health status, patient satisfaction with care, days of restricted activity due to back problems, and costs and utilization of services.

By addressing the methodological shortcomings of previous studies, this trial will clarify the extent to which acupuncture can diminish the effect of chronic low back pain on patient functioning and symptoms. Because chronic back pain is a major public health problem and the top reason patients seek acupuncture treatment, an unambiguous assessment is critical for making informed decisions about the most appropriate role for acupuncture in care for back pain.

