**Figure 1 F1:**
[figure not shown]
Study Design. Process of recruitment, randomization to treatment, treatment provision, and outcomes assessment.

The acupuncture provided will be in accordance with the principles of Traditional Chinese Medicine (TCM) in terms of point selection and needling details. Although many styles of acupuncture are used in the U.S., we selected TCM because it appears to be the most commonly practiced [11,17] is the basis of the national certification exam for non-physician acupuncturists, and is the foundation of non-physician acupuncturist training in the states in which this trial is being conducted. The treatments will be provided by licensed acupuncturists, the group that provides the vast majority of acupuncture treatments in the United States.

In addition to the assigned treatments, all participants will receive a high-quality book about self-management of back pain and will retain access to the health care services to which they are entitled by their insurance coverage.

Participants will be followed for a one-year period following randomization and primary and secondary outcomes will be assessed by telephone interviewers masked to treatment assignment after 8, 26, and 52 weeks. The primary outcome will be dysfunction due to back pain and bothersomeness of back pain. Secondary outcomes will include general health status, satisfaction with back care, days of restricted activity, and use and costs of back-related health care for the year following randomization.

Bias will be minimized by a clinical protocol designed to offer maximum possible masking in a study of a physical procedure such as acupuncture. Although full double masking is not possible, this design permits masking of the assessor of outcomes and substantial masking of participants and the acupuncturist prescribing a treatment. Participants in the three "acupuncture" groups will know only that they will receive one of several methods of stimulating acupoints.

We will perform an intention-to-treat analysis of the data, i.e., the analysis will be by randomized assignment regardless of participation in treatment sessions. This trial was preceded by a pilot trial to assess the feasibility of a full-scale trial. The pilot study demonstrated the feasibility of carrying out a full-scale trial, provided estimates of recruitment rates, follow-up rates, and sample size requirements, and helped us optimize the clinical procedures [18].

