#### d) Usual care

We have included a usual care treatment arm to permit us to determine if individualized or standardized acupuncture offers advantages over standard care for chronic low back pain. Members of this group (as well as members of the three acupuncture treatment groups) will continue to receive the medical care they would have received in the absence of the study. This typically involves continued use of medications (mostly non-steroidal anti-inflammatory medicines), and occasionally, provider visits.

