### Measures of health care resource use

Participants' use of health care for back pain during the year following randomization will be determined from automated utilization data, interview data on out-of-plan utilization, and records for each visit to the study acupuncturists. The automated utilization data provide complete information about all provider visits and hospitalizations at health plan facilities or paid for by the health plan. Visits for back pain can be identified by the diagnosis listed for every visit and hospitalization. Imaging of the lower back can also be identified by specific procedure codes. Our previous studies have found that the automated data are as reliable as chart data for identifying provider visits and imaging for back pain, but much less costly.

Visits to non-study acupuncturists and providers not covered by the health plan will be estimated from the interview data for the time period since the previous interview. In other words, the 8-week interview will request information about out-of-plan utilization since participants were randomized to study treatment, the 26-week interview will ask about the previous 18 weeks, and so forth. To increase the accuracy of response, we will mail participants Health Care Utilization logs to track visits they make for their back pain shortly after randomization and after 8 and 26 weeks. This will permit determination of the percentage of participants in each treatment group who had any visits for low back pain during and following the intervention period, as well as estimation of the mean number of visits. Current use of medications of all types for low back pain will be captured in the follow-up interviews.

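### Some effectiveness ANCOVAs may adjust for back-pain provider visits that, on the natural reading, occur after randomisation and are themselves a trial outcome

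*Protocol article*

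**What the plan says.** Under Statistical analysis, the ANCOVA regresses the follow-up score on its baseline value, three group indicators (usual care is the referent) and a covariate vector z, described as "including geographic site and, for some models, visits to various providers for back pain as part of usual care". The article does not say which models these are or what period the visits cover.

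Other places bear on what those visits are:

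- **Usual care (section d).** Participants in all four arms "will continue to receive the medical care they would have received in the absence of the study".
- **Measures of health care resource use.** On timing, this section states for the health plans' own records: "Participants' use of health care for back pain during the year following randomization will be determined from automated utilization data". Care obtained elsewhere is asked about at each telephone follow-up, and here "the 8-week interview will request information about out-of-plan utilization since participants were randomized to study treatment". The stated use is to compare the "percentage of participants in each treatment group who had any visits for low back pain during and following the intervention period", and mean visit numbers.
- **Background and Overview.** The secondary aims include "days of restricted activity due to back problems, and costs and utilization of services", and the secondary outcomes include "use and costs of back-related health care for the year following randomization".
- **Statistical analysis, on adjustment.** The reason given for adding covariates is precision, and it is framed in terms of pre-treatment variables: "We also plan to adjust for other baseline characteristics". Covariates in the final model are to be picked from past experience and from fit, judged before treatment is added.
- **Abstract.** The primary analysis is an ANCOVA adjusted for the baseline value.

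**The concern.** A covariate in a randomised comparison is safe when assignment cannot have changed it. Visits for back pain during follow-up do not meet that condition. The trial plans to compare them between arms, so it allows that treatment may alter them, and people whose backs are worse plausibly seek more care. Conditioning on such a variable does two things. It removes any part of the treatment effect that works through care-seeking. It also compares participants with equal visit counts who may differ in severity, which randomisation no longer balances.

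The group coefficients in those models would then not answer the question put in the aims. Aim 1, needling against usual care, is the most exposed, because that is where visit rates would most plausibly diverge.

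**Working it through.** **Step 1: timing of the visits.** The sentence that defines z labels the outcome's baseline value as pre-randomisation but gives visits no such label. Usual care is described as care that continues during the trial. Visit measurement is described for the year after randomisation. Table 3 lists non-HMO service use only at 8, 26 and 52 weeks. The cost model omits a baseline value because it is unknown. No pre-randomisation visit count is described as an analysis variable; the earlier primary care visit in Table 1 is an eligibility criterion. Follow-up visits are therefore the natural reading, though an inferred one.

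**Step 2: the plan's own power figures.** Inputs from Sample size and the detectable difference: 160 × 0.9 = 144 per group, adjusted SDs 4.71 and 2.73, critical t 2.61. Power = Φ(δ / (SD × √(2/144)) − 2.61).

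- Roland: SE = 4.71 × √(2/144) = 0.555; 2.0/0.555 − 2.61 = 0.99; power 84%, as stated.
- Bothersomeness: SE = 2.73 × √(2/144) = 0.322; 1.5/0.322 − 2.61 = 2.05; power 98%, as stated.

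Both figures rest on baseline adjustment only and do not involve the visit covariate.

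**Step 3: what adjustment for visits does.** Let D be the total effect of assignment on the Roland score (negative is benefit). Let treatment lower mean visits by *a* within-arm SDs. Let *s* be the within-arm slope of Roland on visits, in points per SD, so that s = r × 4.71 for within-arm correlation r. In the linear model:

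adjusted coefficient = D + a × s = D + a × r × 4.71

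The shift is zero if a = 0, and also if visits are unrelated to outcome within arm. Its sign follows the signs of a and s.

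**Step 4: illustration.** The values of a and r are assumptions; neither is in the documents. Two ranges of r are shown. The lower (0.15 to 0.25) follows if unmeasured severity correlates 0.5 with Roland and 0.3 to 0.5 with visits (0.5 × 0.3 and 0.5 × 0.5). The upper (0.3 to 0.5) assumes the visit–Roland correlation directly. With D = −2.0, the estimated benefit 2.0 − a × r × 4.71 is:

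| a (SD) | r = 0.15 | r = 0.25 | r = 0.3 | r = 0.5 |
|---|---|---|---|---|
| 0 | 2.00 | 2.00 | 2.00 | 2.00 |
| 0.2 | 1.86 | 1.76 | 1.72 | 1.53 |
| 0.5 | 1.65 | 1.41 | 1.29 | 0.82 |

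For example, 0.5 × 0.25 × 4.71 = 0.59, and 2.0 − 0.59 = 1.41. A simulation of 1,000,000 participants under the lower-range structure agreed with the formula to about 0.01 points.

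The sign can reverse. If visits improve the score by 0.5 points per SD and are unrelated to severity, s = −0.5 and the shift is 0.2 × (−0.5) = −0.10 to 0.5 × (−0.5) = −0.25, which overstates the total effect. If treatment has no effect on Roland, the shift itself appears as a false difference: 0.14 to 1.18 points over the table's non-zero rows.

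**The case against.** The strongest reply is that these are extra models. The Abstract defines the primary analysis as adjusted for baseline value, the Statistical analysis section adds baseline characteristics and site, and visits enter only some models built on a general form for any follow-up time. Asking whether other care explains arm differences is a legitimate explanatory question. Much of this stands, and it rules out four stronger readings that a reader might infer.

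- **That the primary 8-week result is biased.** The documents do not show visits in that model. They do not clearly keep them out either: the final covariates are chosen on fit, a visit count that tracks severity could fit well, and judging fit before treatment is added cannot reveal that treatment changes the covariate.
- **That the intention-to-treat commitment is broken.** The article defines it as analysis by randomised group whatever the attendance at sessions. A visit-adjusted model still meets that definition. What changes is the quantity estimated.
- **That the plan contradicts itself on baseline covariates.** It says baseline characteristics will also be adjusted for. It does not say that nothing else may enter any model.
- **That the bias is known, large and always against acupuncture.** It may be zero or reversed. The 4.71 SD is already baseline-adjusted, so r must be the correlation left after baseline severity, and no source supports 0.5. The article calls provider visits under usual care occasional. If 8-week counts were roughly Poisson with mean 0.25 (an assumption), the SD would be 0.5, and a 0.5 SD fall would abolish every visit. The bottom row of the table is then an extreme.

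It is also true that the timing is inferred, and that automated visit data exist from before randomisation, since recruitment uses them. This weakens certainty but does not favour the other reading: no such count is described as a covariate.

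Nor is this merely detail left to an analysis plan. The article positively names an unsuitable covariate.

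**Conclusion.** The point holds for the models that include visits. If the visits are those after randomisation, as the other sections indicate, the group coefficients in those models need not estimate the total effect of assignment. The size cannot be derived from the documents. Under the assumed inputs it runs from an overstatement of 0.25 Roland points, through zero, to an understatement of 1.18, against a target difference of 2.0. The lower-range assumptions cap the understatement at 0.59. The stated power of 84% and 98% is unaffected, and the primary 8-week analysis is exposed only through the loose selection rule. This should be fixed; it does not invalidate the primary analysis as the Abstract describes it.

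**What to change.** In the Statistical analysis section, restrict z, for the primary and every other effectiveness model, to variables measured before randomisation: the baseline outcome, site, other baseline covariates and, if wanted, back-pain visits before randomisation from the automated data. Apply the same limit to the pool from which the final model's covariates are selected. Report visits after randomisation as a utilisation outcome by arm. If a visit-adjusted model is kept, state its time window and label it exploratory and not an estimate of the intention-to-treat effect.

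The cost is about one sentence of analysis wording. It needs no change to sample size, data collection or participant procedures.
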